### Meditation in Spiritual and Secular Contexts

The evidence supporting meditation practice within spiritual contexts’ impact on well-being is much less developed than for secular interventions, probably because the latter are easier to incorporate into countries’ modern institutional settings. While spiritual and secular Buddhist meditation practices look similar, their contexts are often quite different, which may lead to different outcomes. Spiritual traditions usually integrate their philosophy or teachings into their practice, which may influence how practitioners engage with meditation. Spiritual traditions often recommend practitioners practice within moral guidelines like precepts as supports for practice and use exemplars (the Buddha or teachers) to orient practitioners [26,27]. Spiritual contexts also offer communities of practice, regular meditation classes, and dedicated practice spaces to support practitioners’ regular meditation after initial instruction; these are absent in most secular settings. Moreover, while secular programs, such as MBPs, are explicit about their aim to cultivate health and well-being, traditional forms of Buddhist meditation do not primarily aspire to produce health and well-being outcomes as their central goal [28]. Instead, they aim for spiritual liberation, insight into the nature of reality, and freedom from suffering (dukkha) in the Buddhist sense [29]. Increased quality of life and mental well-being are still to be expected as a side effect or fruit along the path; however, and are sought after by many contemporary spiritual practitioners [3].

While there is some evidence of well-being and mental health benefits from spiritual meditation practices [30], to our knowledge there is no longitudinal empirical evidence on the long-term effects of prolonged spiritual meditation practice. A cross-sectional survey by our team including both secular and spiritual meditation practitioners with varying lifetime practice history found a dose-response plateau between historical practice hours and psychological well-being outcomes after 500 hours of practice [31]. This survey also found that meditating at a regular time each day was associated with positive outcomes, supporting the hypothesis that regularity of practice may be more impactful than intense but irregular sets. Follow-up surveys at 2 months and 2-4 years with this same sample found both practice dose, that is, hours per month, and practice frequency significantly predicted improvements in life satisfaction, affect, and psychological distress [32]. However, these participants’ varying lifetime practice history introduces possible survivor bias effects (ie, only those who had already been benefiting from regular practice over the years signed up to complete these surveys) and obscures the effects of initiating a regular practice. Moreover, this study was not preregistered, included very heterogeneous types of meditation practice, and used a rough estimate of practice during the 2-4 year follow-up. To address these gaps, a preregistered longitudinal study focused on those initiating a regular practice is required.

To our knowledge, there is only one study that compares the outcomes of an explicitly spiritual meditation practice to a control group that includes secular meditation practices [33]. In this study of 31 participants, a program (Dharma in Daily Life) that emphasized both regular meditation and integration of Buddhist teachings showed greater improvement in subjective well-being (but not quality of life) than continued meditation practice as usual over a 2-year intervention period. However, while the meditation as usual group included secular practices, it also contained participants who engaged in some other spiritual meditation practices (eg, Vipassana and Zen), and all participants in both groups had some familiarity with Buddhism. A further study is necessary to disentangle the potential moderating effects of spiritual and secular meditation contexts on quality of life and mental well-being.

### Cost-Effectiveness of Meditation

If effective, regular meditation could form the basis of scalable and accessible public health interventions, as it requires relatively few economic resources [34]. Previous research shows some evidence that MBPs are generally cost-effective compared to usual care, specifically for quality of life and mental health [34-36], though there are some exceptions [37]. Moreover, it has been argued that the cost-effectiveness of MBPs may rely on practice adherence and may only be sustained with ongoing practice over time [35,36,38]. Since most studies have not taken into account whether the participants continue their practice after initial program completion or measured their ongoing meditation-related costs, it is yet to be established whether continued meditation practice is required to maintain cost-effectiveness [35,36]. To inform public and individual health decision-making, a longitudinal study that monitors continued meditation practice after initial instruction, as well as its associated costs and effects, is needed.

### Adverse Effects

There is growing recognition that for some practitioners, regular meditation practice can lead to harm [39-41]. Previous studies have documented a wide range of intense and unexpected experiences as a result of meditation practice, such as strong emotions, traumatic re-experiencing, and altered perceptions [42,43]. Such experiences can generate functional impairment and sometimes become clinically relevant [44]. Intense and unpleasant experiences are estimated to be encountered by 31%‐58% of meditation practitioners, depending on the measurement instrument, with about 9% of practitioners experiencing functional impairment [41]. There is some evidence indicating that adverse effects occur more often after initial instruction, in periods when secular practitioners typically have less or no support from teachers and peers [45]. Indeed, incidences of unpleasant and adverse effects are more commonly reported by practitioners with prolonged practice [41,42,44].

These findings have raised crucial questions about how frequently, and for whom, harm is experienced in meditation practice. Current evidence on the adverse effects of regular meditation practice comes from cross-sectional studies, which do not allow effects to be captured accurately due to memory and self-selection biases [44] or for their specific context or timing to be documented [46]. To address these concerns, a longitudinal study that assesses the incidence and impact of meditation-related adverse experiences as they arise during regular practice is needed.

### This Study

This study seeks to investigate the long-term effects of meditation practice on quality of life and well-being in current ecological contexts through longitudinal examination of a cohort of beginner meditators who intend to continue practicing over one year. Specifically, this study aims to estimate the effectiveness of regular meditation practice after initial instruction for promoting quality of life (Aim 1, primary outcome) and mental well-being (Aim 2). We hypothesize that the amount of regular meditation practice during approximately the first year after initial instruction will predict practitioners’ quality of life, such that more regular practice predicts greater quality of life (Hypothesis 1). We also hypothesize that the amount of regular meditation practice during approximately the first year after initial instruction will predict practitioners’ mental well-being, such that more regular meditation will predict greater mental well-being (Hypothesis 2).

The study further aims to test whether the meditation tradition being secular or spiritual moderates any effects on quality of life (Aim 3). We hypothesize that whether participants’ meditation practice is predominantly secular or includes engagement with spiritual practices will moderate any effects on quality of life (Hypothesis 3, nondirectional). We further aim to test whether the meditation practice being secular or spiritual moderates any effects on mental well-being (Aim 4). Mental well-being captures the flourishing spectrum of mental health, and there may be moderation effects detectable in this domain that would not be evident for quality of life [33], either due to a lack of effect or because those relationships are obscured by potential ceiling effects in negatively worded quality of life measures. We hypothesize that whether the meditation tradition is secular or spiritual will moderate any effects on mental well-being (Hypothesis 4, nondirectional).

The study also aims to explore the cost-effectiveness of regular meditation practice on quality of life (Aim 5). Given that this is a cohort study and we will not have a control group as we would in an RCT, we will conduct an exploratory economic analysis using a comparator group of those not continuing with meditation compared to those that are, accounting for confounding factors.

Finally, the study aims to document the incidence and impact on daily function of any challenging, difficult, or distressing meditation-related experiences (Aim 6). Meditation-related adverse effects (MRAEs) will be defined as any challenging, difficult, or distressing meditation-related experiences that impact everyday functioning. Our aims, hypotheses, and possible interpretations are summarized in Table 1 below.

**Table 1. T1:** Protocol Design table.

Question	Hypothesis	Sampling plan (eg, power analysis)	Analysis plan	Interpretation given to different outcomes
Does regular meditation practice after initial instruction increase quality of life?	The amount of meditation practice during approximately the first year predicts practitioners’ quality of life, such that a greater amount leads to greater quality of life.	A total number of 522 gives 95% power to detect the variance in quality of life (EQ-HWB-9^a^) explained by monthly meditation practice observed in linear mixed model analysis, at a 2-tailed significance level of 0.05, accounting for an estimated 20% loss to follow-up.	Linear mixed model of the fixed effect of the amount of meditation in the past month on quality of life in the past week (EQ-HWB-9), controlling for the confounding factors of age, caring status, education, mental health diagnosis, commitment to meditation, and membership of a practice support community at baseline.	A positive/negative and statistically significant association between the amount of meditation in the past month on quality of life and in the past week will suggest that regular meditation practice after initial instruction increases/decreases quality of life in a linear fashion. A nonsignificant association will suggest an absence of evidence for either of these effects.
Does regular meditation practice after initial instruction increase mental well-being?	The amount of meditation practice during approximately the first year predicts practitioners’ mental well-being, such that a greater amount leads to greater mental well-being.	A number of 242 gives 95% power to detect the variance in mental well-being (SWEMWBS^b^) explained by monthly meditation practice observed in linear mixed model analysis, at a 2-tailed significance level of 0.05, accounting for an estimated 20% loss to follow-up.	Linear mixed model of the fixed effect of the amount of meditation in the past month on mental well-being in the past 2 weeks (SWEMWBS), controlling for the confounding factors of age, caring status, education, mental health diagnosis, commitment to meditation, and membership of a practice support community at baseline.	A positive/negative and statistically significant association between the amount of meditation in the past month on mental well-being in the past 2 weeks will suggest that regular meditation practice after initial instruction increases/decreases mental well-being in a linear fashion. A nonsignificant association will suggest an absence of evidence for this.
Is the effect of continued meditation practice after initial instruction on quality of life moderated by whether a practitioner’s meditation tradition is spiritual or secular?	Whether the meditation tradition is secular or spiritual will moderate any effects on quality of life (nondirectional)	Sampling plan follows hypothesis 1, with an additional 20%, n=627, powered to detect effect of f^2^=0.0318	Linear mixed model of the fixed effect of the amount of meditation in the past month and the interaction effect of tradition spirituality on quality of life in the past week (EQ-HWB-9), controlling for the confounding factors of age, caring status, education, mental health diagnosis, commitment to meditation, and membership of a practice support community at baseline.	A positive/negative statistically significant beta coefficient for this interaction will indicate that regular meditation practice within a spiritual tradition will have a larger/smaller effect on quality of life than practicing within a secular tradition. A nonsignificant association will suggest absence of evidence for this.
Is the effect of continued meditation practice after initial instruction on mental well-being moderated by whether a practitioner’s meditation tradition is spiritual or secular?	Whether the meditation tradition is secular or spiritual will moderate any effects on mental well-being (Hypothesis 4, nondirectional).	Sampling plan follows hypothesis 2, with an additional 20%, n=291, powered to detect effect of f^2^=0.045	Linear mixed model of the fixed effect of the amount of meditation in the past month and the interaction effect of tradition spirituality on mental well-being in the past 2 weeks (SWEMWBS), controlling for the confounding factors of age, caring status, education, mental health diagnosis, commitment to meditation, and membership of a practice support community at baseline.	A positive/negative statistically significant beta coefficient for this interaction will indicate that regular meditation practice within a spiritual tradition will have a larger/smaller effect on mental well-being than practicing within a secular tradition. A nonsignificant association will suggest absence of evidence for this.
What is the association between the costs and outcomes of meditation practice?	No hypothesis	Our sampling plan will follow hypothesis 1.	We will conduct an exploratory cost-effectiveness analysis to compare effects (quality of life) with a range of costs (costs of mental health support, costs associated with meditation practice)	Results will be presented as an ICER^c^ with associated sensitivity analysis, as outlined above.
What is the incidence and functional impact of meditation-related adverse effects	No hypothesis	—^d^	Proportion and CIs of the frequency, severity of impairment on daily function, and duration of impairment of initial meditation-related challenging experiences and adverse effects (MRAEs)	—

a EQ-HWB-9: 9-item EuroQoL Health and Wellbeing.

b SWEMWBS: Short Warwick-Edinburgh Mental Well-Being Scale.

c ICER: incremental cost-effectiveness ratio.

d Not applicable.

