For hypothesis 4, we will add the secular versus spiritual variable and its interaction term with the amount of meditation to the model for hypothesis 2.

To address aim 5, we will conduct an exploratory cost-effectiveness analysis using participants who did not continue meditating as a comparator to participants with ongoing meditation practice, while accounting for relevant confounding factors. We will use the EQ-HWB-9 to measure outcomes, applying index values from the United Kingdom pilot value set over time to create QALYs [60]. Costs will include those for mental health service use (psychological support) across one year plus costs of meditation practice. To calculate the incremental cost-effectiveness ratio (ICER) from a public health perspective, we will calculate the difference in costs between the low- and high-meditation dosage groups and divide by differences in QALYs. The ICER represents the additional cost of the intervention for each additional unit of health benefit gained. We will investigate the cost-effectiveness of the ICER against thresholds of the 4 included countries, as available, to determine how likely the intervention will be cost-effective from a public health perspective. Issues of confounding will be addressed through statistical adjustments as per the main analysis, and we will conduct relevant scenario analyses. We will conduct deterministic (one-way) sensitivity analysis to estimate the impact of uncertainty around effects by varying output and cost parameters, displayed on tornado graphs. We will conduct probabilistic sensitivity analysis to explore the combined parameter uncertainty over 10,000 iterations, displayed on a cost-effectiveness plane.

To address aim 6, we will estimate the incidence of participants first reporting adverse effects by reporting the proportion and confidence intervals of first adverse experiences that also impaired participants’ daily function. We will also report descriptive statistics of the frequency, severity of impairment of daily function, and duration of impairment of meditation-related challenging experiences and MRAEs.

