The study also aims to conduct an economic evaluation in the form of an exploratory cost-effectiveness analysis to investigate costs and outcome comparisons associated with regular meditation practice. As this study is a cohort study and not an RCT where we would usually see cost-effectiveness analysis conducted, and as there is no control group, we plan to construct an exploratory cost-effectiveness analysis using a comparator group of those not continuing to meditate. This is a major limitation to the cost-effectiveness analysis proposed in this study.

There are further limitations regarding effects and costs. Although the EQ-HWB-9 has been shown to be valid for measuring quality of life in people who meditate [76], there are currently no country-specific value sets for the EQ-HWB-9 for Australia, New Zealand, or the United States. We will have detailed information on costs due to psychological care; however, we will need to estimate costs from this information for the relevant country’s health systems where costs are not out-of-pocket. This analysis is further exploratory on the basis of the direction of the effect. For instance, if, through partaking in meditation practice, participants decide to pursue mental health support, this will increase costs but may also increase outcomes. Hence, lowering mental health support costs may not be the objective here. We acknowledge the potential opportunity cost of meditation practice, and while we will be able to provide information on the time commitment needed to achieve benefit in our primary analysis, we are unable to address this in the current exploratory cost-effectiveness analysis. As the outcomes look at change in QALYs over one year, we will also not be able to take into account changes in effects and costs during this period for the base analysis. We may be able to do further exploratory analysis investigating the associations between costs and effects over time in a future study.

Finally, the study aims to estimate the incidence of MRAEs. We anticipate the incidence of MRAEs will be around 10%, in line with previous research [42]. We also expect the average impact on daily function to be small, on average, but that some participants will experience significant impairment to daily function. We plan to conduct a future mixed methods examination of MRAEs to explore their predictors and phenomenology.

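### Aim 5 groups people by practice after baseline and compares QALYs and costs over that same year with baseline adjustment only, so any influence of quality of life on stopping biases the ICER in an undetermined direction

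*Protocol article*

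**What the plan says.** The section This Study introduces Aim 5 as a comparison "using a comparator group of those not continuing with meditation compared to those that are", with confounding to be accounted for. The Analysis Plan repeats this as an analysis "using participants who did not continue meditating as a comparator to participants with ongoing meditation practice". For the ICER itself the Analysis Plan names a different pair of groups: "we will calculate the difference in costs between the low- and high-meditation dosage groups and divide by differences in QALYs".

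The outcome window is the year of follow-up. On costs: "Costs will include those for mental health service use (psychological support) across one year plus costs of meditation practice". QALYs come from EQ-HWB-9 index values over time, and the Discussion describes them as a one-year quantity. It adds that "we will also not be able to take into account changes in effects and costs during this period for the base analysis".

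On confounding: "Issues of confounding will be addressed through statistical adjustments as per the main analysis", together with scenario analyses whose content is not given. The main analysis (Hypothesis 1) lists baseline covariates only: age, education, caring role, diagnosis history, commitment and community membership. For Hypotheses 1 and 2 the plan adds inverse probability weighting of monthly practice, to allow for earlier practice and earlier gains. That is a sensitivity analysis, run only if an effect is detected, and it is not stated for Aim 5.

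**The concern.** Intention to continue is an entry criterion, so nobody is a non-continuer at baseline. The status can only be learned from follow-up, and so can low or high dosage. The groups and the outcome therefore share one window, with two consequences.

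- **QALYs.** If a change in quality of life leads someone to stop, that change lies inside the QALY total and is read as a result of stopping. Baseline covariates cannot remove it, because it arises after baseline.
- **Costs.** Meditation spending and mental health care before stopping are booked to the non-continuing group, although they belong to months of practice.

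Both parts of the ICER are affected. The plan will set the ICER against the cost-effectiveness thresholds of the four countries, and that reading inherits the bias.

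**Working it through.** The document gives no Aim 5 figure (no size, power, QALY difference or ICER), so there is nothing to reproduce. The check asks whether the planned contrast returns zero when the true effect is zero.

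**1. QALY scale, all inputs assumed.** Monthly utility is a person effect (SD 0.15) plus a within-person part (SD 0.10, monthly autocorrelation 0.7), over 12 months, with no effect of practice. The monthly stopping hazard is 0.04 × exp(b × z), where z is the number of SDs by which utility is worse than average. Whole-year QALY is regressed on continuing status and baseline utility.

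| b per SD worse utility | Continuers minus stoppers, QALY |
|---|---|
| +0.4 (worse utility raises stopping) | +0.020 |
| -0.4 (worse utility lowers stopping) | -0.019 |

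The true value is zero in both rows. At 3-5% stopping per month, slopes of +0.2 and +0.6 gave about 0.008-0.011 and 0.027-0.034. Baseline utility is not among the covariates listed for Hypothesis 1, so adjusting for it favours the plan. With no utility adjustment, slopes of +0.2, +0.4 and +0.6 gave 0.033-0.037, 0.065-0.071 and 0.096-0.102. The listed covariates would remove part of that, by an amount that cannot be computed from the document.

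**2. Score scale.** Inputs: SD 7.0 from the Sampling Plan; half stop within the year (the Introduction's estimate that about half continue after a course, assumed to apply here); score oriented so that higher is better. Stopping depends on the previous month's score. Within-person variance share (30-50%) and autocorrelation (0.5-0.8) are assumed.

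| Odds ratio of stopping per 7 points worse | Unadjusted difference | Adjusted for baseline score |
|---|---|---|
| 1.0 | about 0 | about 0 |
| 1.25 | 1.3-1.6 | 0.45-0.60 |
| 1.5 | 2.2-2.8 | 0.80-1.05 |
| 2.0 | 3.6-4.4 | 1.34-1.77 |

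For scale, the Sampling Plan's change for the moderate group is 2.25 points. At an odds ratio of 1.5 the false difference is 0.80/2.25 = 36% to 1.05/2.25 = 47% of it.

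**3. Costs.** At constant monthly hazards of 3% and 5%, stoppers stop on average at months 6.1 and 5.9. About half of a stopper's year (6/12) is thus practising time counted in the non-continuing group.

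**4. What removes the bias.** On the score scale, a month-6 landmark adjusted for baseline score only still shows 0.28-1.04 points at odds ratios of 1.25-2.0. Weighted on score history before stopping, it shows -0.04 to 0.06. Those weights used the known stopping model, so this is the best case.

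**5. What should not be done.** Regression on utility measured while practice status is being set removes real benefit. Take a true effect of 0.03 utility while practising, stopping unrelated to utility, and 4% stopping per month:

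| Landmark | Most that could be seen | Adjusted for baseline utility only | Adjusted for utility up to the landmark |
|---|---|---|---|
| Month 3 | 0.03 × 9/12 = 0.0225 | 0.018 | 0.005 |
| Month 6 | 0.03 × 6/12 = 0.015 | 0.013 | 0.003 |

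The loss is 1 - 0.005/0.018 = 72% at month 3 and 1 - 0.003/0.013 = 77% at month 6.

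**6. Dilution in a landmark.** At 4% per month, 1 - 0.96^12 = 38.7% stop within the year and 1 - 0.96^3 = 11.5% by month 3. So 11.5/38.7 = 30% of eventual stoppers are classed as stopped, and the other 70% count as ongoing.

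**The case against.** The strongest reply is that Aim 5 is called exploratory throughout, has no hypothesis, and has its constructed comparator disclosed as a major limitation. The Discussion also admits that changes within the year are left out of the base analysis. The authors know about feedback from benefit to practice, because they plan weighting for it under Hypotheses 1 and 2. The unspecified scenario analyses might cover it, and the exact rule for who counts as not continuing may properly sit in a fuller plan.

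Much of this stands, and it limits the severity. It does not answer the point. The disclosure concerns the absence of a control group and does not mention that quality of life may drive stopping. The comparator, the window and the adjustment are choices the article states. EQ-HWB-9 and costs are collected monthly, so the within-year information exists.

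Two stronger readings are tempting, and the documents support neither.

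- A reader might infer that the ICER will credit meditation with a false gain. The document does not say that falling quality of life leads to stopping. People who feel better may stop, and distressed people may practise more; the sign then reverses.
- A reader might turn the simulated differences into a high false-positive rate. Aim 5 runs no significance test. It reports an ICER, one-way and probabilistic sensitivity analyses and a cost-effectiveness plane, so a rejection rate describes nothing in the plan.

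**Conclusion.** The point holds as a timing problem. Under either contrast the groups are formed by behaviour after baseline, the QALYs and costs cover the same year, and the stated adjustment uses baseline factors only. If quality of life during the year affects stopping, the ICER is biased, in a direction and by an amount the document does not determine.

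About 0.02 QALY in either direction is an illustration. It rests on an assumed log-hazard of 0.4 per SD, assumed utility SDs and 4% stopping per month. With no link between quality of life and stopping, the QALY bias vanishes, but the misattribution of costs incurred before stopping remains. The analysis should be changed before the ICER is read against thresholds; because Aim 5 is exploratory, the primary analysis is not affected.

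**What to change.** - Choose one contrast, either not continuing versus ongoing or low versus high dosage, as the basis of the ICER, and use it throughout.
- Extend the inverse probability weighting planned for Hypotheses 1 and 2 to Aim 5, whether or not an effect is detected. Weight each month's practice status on baseline EQ-HWB-9 utility and on utility, practice and mental-health-care cost recorded before that month.
- Compute weighted QALY and cost differences, attributing both by time of practice.
- Do not adjust by regression for utility measured after practice status is set.
- Report the unweighted whole-year contrast as description, and state that feedback from quality of life to practice may bias it in either direction.
- Optionally add a landmark scenario: groups set by month 3, outcomes from month 3 to month 12, weighted on history before stopping. State that later stoppers count as ongoing, which dilutes the contrast.

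The data needed are already scheduled, and collection is still under way. The cost is more analysis work and wider intervals from the weights. Weighting gives no protection against causes of stopping that are not recorded.
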